### Eligibility criteria

The target population for the ASTuTE trial is adults with prostate adenocarcinoma and IR per the NCCN risk classification [22]. Potential participants will be screened for eligibility according to the inclusion and exclusion criteria outlined in Table 1.

**Table 1 Tab1:** Eligibility criteria

Inclusion criteria	Exclusion criteria
1. Adult males > 18years of age	1. Participants who have already commenced ADT or inability to receive ADT.
2. Participants must have intermediate risk, localised adenocarcinoma of the prostate according to NCCN risk Favourable intermediate risk (FIR): • 1 intermediate risk factor (IRF) • Grade Group 1 or 2 (Gleason Score ≤ 6 or Gleason Score 7 {3 + 4}) • < 50% biopsy cores positive (e.g., < 6 of 12 cores) Unfavourable intermediate risk (UIR) • 2 or 3 IRFs • Grade Group 3 (Gleason Score 7) • ≥ 50% biopsy cores positive (e.g., ≥ 6 of 12 cores) IRFs: • Clinical stage cT2b-cT2c • Grade Group 2 or 3 (Gleason Score 3 + 4 = 7 or 4 + 3 = 7) • PSA 10-20ng/mL	2. Participants with insufficient tissue and/or histopathology issues which may arise pertaining to the generation of an accurate ArteraAI Prostate Test result.
	3. Participants with histological or cytological evidence of neuroendocrine or small cell differentiation.
	4. Prostate adenocarcinoma that cannot be International Society of Urological Pathologists (ISUP) graded.
	5. High risk clinical features (PSA > 20, Grade Group 4–5, Stage T3-4). Node positive or presence of distant metastases (cN1 or cM1).
3. Estimated life expectancy > 10 years	
4. Participants must be planned to undergo curative-intent radiotherapy for prostate cancer	
5. Willing and able to provide written informed consent	

### Methods

After providing informed consent, clinical variables including combined Gleason score, Primary Gleason Score, Secondary Gleason Score, clinical T-stage, baseline PSA, and age at biopsy are recorded. Next, a single formalin fixed, paraffin embedded (FFPE) hematoxylin and eosin-stained slide containing one biopsy core with the tumor that has the highest Gleason grade used by the local pathologist in making their diagnosis for the patient will be digitised.

When scanning is completed, a certified pathologist approved by Artera^®^ will review the digitally converted image to assess suitability for the MMAI biomarker test. The test will be run using locked AI models (v1.2) for the duration of the study. The locked models makes sure all participants will be assessed using the same models [23]. After completion of the test, the ArteraAI Prostate Test report will be verified by the certified pathologist and then made available to clinical staff via a web portal.

Figure 3 shows an example of the test report. Figure 3a displays an example of an NCCN unfavourable IR prostate cancer who is estimated to have a low prognostic risk for distant metastasis and low predictive benefit for the addition of ADT with radiotherapy using the ArteraAI Prostate Test. Figure 3b displays the other side of the spectrum with the ArteraAI Prostate Test estimating a high prognostic risk for distant metastasis and high predictive benefit for the addition of ADT with radiotherapy. Before the test result is available, the pre-test shared ADT decision result is captured. After the ArteraAI Prostate Test results are discussed between the clinician and patient, the post-test shared ADT decision result will be recorded. At a median follow-up of 5 years for the cohort, a data linkage with PCOR will be established to allow for assessment of quality of life and efficacy data (Table 2).

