**Methods:**

This multicentre implementation trial aims to collect real-world data on the use of the previously validated Artera MMAI-driven prognostic and predictive biomarkers in men with intermediate-risk prostate cancer undergoing curative radiotherapy. The prognostic biomarker estimates the 10-year risk of metastasis, while the predictive biomarker determines the likely benefit from short-term ADT (ST-ADT). A total of 800 participants considering ST-ADT in conjunction with curative radiotherapy will be recruited from multiple Australian centers. Eligible patients with intermediate-risk prostate cancer, as defined by the National Comprehensive Cancer Network, will be asked to participate. The primary endpoint is the percentage of patients for whom testing led to a change in the shared ST-ADT recommendation, analyzed using descriptive statistics and McNemar’s test comparing recommendations before and after biomarker testing. Secondary endpoints include the impact on quality of life and 5-year disease control, assessed through linkage with the Prostate Cancer Outcomes Registry. The sample size will be re-evaluated at an interim analysis after 200 patients.

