### Endpoints

The primary objective is to assess the impact of the ArteraAI Prostate Test on shared ST-ADT decisions with IR prostate cancer men undergoing curative radiotherapy. To evaluate this, the endpoints of shared ST-ADT decisions pre-test and post-test will be recorded. The primary endpoint is the percentage of cases with changes in ST-ADT shared decision recommendations.

The secondary objectives will be assessed through linkage with the Prostate Cancer Outcomes Registry (PCOR) and will assess efficacy and quality of life. The secondary endpoint of efficacy will be assessed at 5 years using the Phoenix criteria of PSA nadir + 2ng/mL [21], and/or initiation of salvage treatment and/or imaging confirming recurrent disease. The secondary endpoint of quality of life will be assessed using the Expanded Prostate Cancer Index Composite questionnaire (EPIC-26).

The primary hypothesis is that the ArteraAI Prostate Test will result in changes to ADT management of IR prostate cancer patients. The secondary hypotheses are that this will be accompanied by ongoing high rates of disease control and improved quality of life for those spared ADT.

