**Fig. 3 Fig3:**
[figure not shown]
**a and b.** ArteraAI Prostate Test report examples. Green box highlighting the prognostic model score and Blue box highlighting the predictive model result for ADT benefit

**Table 2 Tab2:** Schedule of assessments (according to SPIRIT-AI extension)

	Enrolment / Pre-test^1^	Post-test^2^	5-year follow-up
1. Demographics	X		
2. Prostate cancer history	X		
3. Shared ADT decision recommendation as determined by primary clinician and participant	X	X	
4. EPIC-26 Quality of Life questionnaire	X^*3*^		X^*3*^
5. Disease Control			X^*3*^

^*1*^
*Enrolment / pre-test can happen over a period of 14 days*

^*2*^
*Post-test data collection may occur at initial consult if ArteraAI Prostate Test results are available*

^*3*^
*Data linkage through Prostate Cancer Outcomes Registry at median 5-year follow-up.*

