### Statistical considerations

Given the novel nature of ASTuTE, it is not possible to estimate the event rate for the primary endpoint proportion change in shared decision making regarding use of ADT. If an incorrect estimate is used, there is a risk of underpowering the study. Therefore, an interim analysis will be performed at 200 participants. This will allow for early assessment into the rates of management change and help determine the final number of participants needed to adequately power the final analysis of the study. At this time, 800 participants are planned for enrolment, with final numbers to be determined at the time of the interim analysis.

The McNemar’s test will be used to analyse the primary endpoint. There is a rare chance that the number of pre- to post-test recommendations of Yes-No and No-Yes is equal. This could lead to the null hypothesis being retained when the ArteraAI Prostate test is actually outperforming standard of care. As such, the study is designed to be hypothesis-generating, rather than focusing on a specific hypothesis that would define the sample size. This trial of implementation which assesses rates of management change based on a biomarker test has been used in recent literature. The DCISionRT^®^ study, used this approach to assess a breast genomic biomarker impact on radiation therapy recommendations [24].

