**Fig. 4 Fig4:**
[figure not shown]
2 × 2 contingency table illustrating McNemar’s test for paired data to assess rates of change for the biomarker test, ArteraAI Prostate Test, on shared ADT decision making. Primary endpoint of proportion changing shared decision on use of ADT is calculated as (b + c) / (a + b + c + d)

Multivariate logistic regression analyses will also be used to assess the odds ratios (OR) of factors leading to the pre-test and the post-test ADT recommendations. Pre-test exploratory covariates can include age, ISUP grade, initial PSA, tumour stage and percentage of cores positive. Post-test covariates will also include the ArteraAI Prostate test results.

The study opened to enrolment in December 2023, and is expected to complete accrual in 2025.

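### The only stated registry extract is timed to a cohort median of 5 years, so up to about half the men cannot yet have the 5-year EPIC-26 score scheduled in Table 2

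*Protocol article*

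**What the plan says.** The Methods section gives the trigger for obtaining the secondary outcome data: "At a median follow-up of 5 years for the cohort, a data linkage with PCOR will be established". Footnote 3 to Table 2 repeats it: "Data linkage through Prostate Cancer Outcomes Registry at median 5-year follow-up". That footnote is attached to the disease control entry and to both EPIC-26 entries, baseline and follow-up.

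The time point of the endpoints is given in three places:
- Endpoints section: "The secondary endpoint of efficacy will be assessed at 5 years using the Phoenix criteria of PSA nadir + 2ng/mL", with salvage treatment and imaging recurrence as further components. EPIC-26 is named there without a time.
- Abstract, Methods: "Secondary endpoints include the impact on quality of life and 5-year disease control, assessed through linkage with the Prostate Cancer Outcomes Registry".
- Table 2: the row "EPIC-26 Quality of Life questionnaire" is marked at enrolment and in the 5-year column. Disease control is marked in the 5-year column only.

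The Data analysis plan section says that the study opened in December 2023 and "is expected to complete accrual in 2025". On size, Statistical considerations says that "800 participants are planned for enrolment, with final numbers to be determined at the time of the interim analysis".

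The article states no second linkage, no minimum follow-up and no window for the 5-year questionnaire.

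**The concern.** A median trigger and a fixed 5-year assessment do not fit together when entry is staggered. When half the cohort has passed 5 years, the other half has not. A man below 5 years can be censored in a time-to-event analysis of disease control. A questionnaire score at 5 years has no such remedy: if the date has not come, the score does not exist, and no later analysis choice can supply it.

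At stake is the precision of the EPIC-26 endpoint. It carries the secondary hypothesis that men who avoid ADT have better quality of life, which concerns only part of the cohort. The men affected are those enrolled last. They are selected by calendar time and not by outcome, so the loss is mainly one of precision. It would become a bias only if the case mix or the use of the test drifted over the accrual period.

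**Working it through.** The article states no number reaching 5 years, so there is no figure to reproduce. The check uses the definition of a median and a range of accrual patterns.

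**Inputs**
- Trigger: cohort median follow-up of 5 years (Methods; Table 2, footnote 3).
- Planned N: 800, provisional (Statistical considerations). The percentages below do not depend on N.
- Accrual length A: December 2023 to some point in 2025, about 13 to 25 months (Data analysis plan).
- Accrual shape, death or loss rate, and EPIC-26 window: not stated. They are assumed below, with ranges.

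**Step 1: follow-up at the extract, uniform accrual.** The median man enters at A/2, so the extract falls A/2 + 5 years after the first entry. A man entering at time e has 5 + A/2 − e years, so follow-up runs from 5 − A/2 to 5 + A/2.
- A = 13 months: 4.46 to 5.54 years.
- A = 24 months: 4.0 to 6.0 years.
- A = 25 months: 3.96 to 6.04 years.

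In each case 400 of 800 men (50%) are below 5 years. Accelerating and front-loaded accrual also give 400 of 800. The shortest follow-up in any pattern tried is 3.58 years (25 months, front-loaded).

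**Step 2: if the median is of observed follow-up.** Deaths and losses then make up part of the lower half. With uniform accrual and an assumed yearly death or loss hazard, the share short of 5 years because of the extract date is:

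| Yearly hazard | Short because of extract date |
|---|---|
| 0% | 50% |
| 1% | 47% |
| 2% | 45% |
| 5% | 36% |
| 10% | 17.5% |

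**Step 3: EPIC-26 precision.** If a fraction p of the men who would otherwise have a 5-year score can have one at the extract, the standard error is multiplied by 1/√p. With uniform accrual and scores accepted from w years before the 5-year date, p = 0.5 + w/A, up to a maximum of 1.

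| Accrual | Window w | p | Rise in SE |
|---|---|---|---|
| any | none | 0.50 | 1/√0.50 = 1.41, about 41% |
| 24 months | 6 months | 0.5 + 0.5/2 = 0.75 | 1/√0.75 = 1.15, about 15% |
| 18 months | 6 months | 0.5 + 0.5/1.5 = 0.83 | 1/√0.83 = 1.10, about 10% |
| 13 months | 6 months | 0.5 + 0.5/1.083 = 0.96 | 1/√0.96 = 1.02, about 2% |
| 24 months | 12 months | 1.00 | none |

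Short accrual helps only together with a window. With no window the share stays at one half whatever the accrual length. Under the observed-follow-up reading with a 2% hazard and no window, p = 1 − 0.45 = 0.55 and the rise is 1/√0.55 = 1.35, about 35%.

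**Step 4: disease control with censoring.** This uses 25-month uniform accrual, N = 800 and the Greenwood approximation, with assumed 5-year control:

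| Control at 5 years | SE, median trigger | SE, all reach 5 years |
|---|---|---|
| 85% | 0.0132 | 0.0126 |
| 90% | 0.0110 | 0.0106 |
| 95% | 0.0080 | 0.0077 |

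At 90% control about 360 rather than 720 men are at risk at 5 years, but the standard error hardly changes.

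**Step 5: delay until the last man reaches 5 years.** Under uniform accrual this is A/2, that is 0.54 to 1.04 years. Across all shapes tried it is 0.32 to 1.43 years.

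**The case against.** The best defence is that the passages describe one loosely worded design: report the secondary outcomes once the cohort has a median of 5 years. The article nowhere says that the endpoint is defined at each man's own fifth anniversary. For EPIC-26 the 5-year tie is only a column heading in Table 2, qualified by a footnote that repeats the median. This has force, but footnote 3 also marks the baseline questionnaire, so it reads as an extract date and not as an assessment time. The column still says 5 years.

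Three stronger readings are tempting and are not supported.

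- **That the 5-year disease control rate will be overstated.** This would need a crude percentage that counts men with short follow-up as controlled. The article fixes no such estimator. It speaks only of summary statistics, which can include a Kaplan-Meier estimate, and the choice may properly sit in the SAP. Even a crude rate would understate failure by only 0.24 to 0.83 percentage points, for assumed hazards of 1% to 4% per year and 24-month uniform accrual.
- **That half the quality-of-life data are lost outright.** The 41% figure requires that no score before exactly 5.0 years be usable. The article neither states a window nor rules one out, and it does not say when the registry administers the questionnaire.
- **That there will be only one extract.** None beyond the first is stated, but none is excluded, and the full protocol may provide for one.

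The study also calls itself hypothesis-generating, and these are secondary endpoints. That limits the weight of the point. It does not remove the mismatch between the stated trigger and the stated schedule.

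**Conclusion.** The point holds in limited form. As written, the only stated extract comes when up to about half the men are administratively short of 5 years. The share is lower if the median is of observed follow-up, for example 45% at an assumed 2% yearly death or loss hazard. Under uniform accrual the shortfall per man is at most about 0.5 to 1.0 year.

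The consequence falls on EPIC-26. Its standard error is larger by anything from almost nothing (a wide window, or short accrual with a 6-month window) to at most about 41% (no window). About 15% is a reasonable middle case, for 24-month accrual and a 6-month window. Disease control loses little precision under a censored estimate, and a reader should not infer a biased control rate from the article. The primary endpoint is unaffected.

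The one-half figure follows from the definition of a median. The other sizes rest on assumed accrual shape, window and loss rates, none of which the article gives.

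**What to change.** - Keep the linkage at a median of 5 years if an earlier report is wanted, but add a repeat extract when the last enrolled participant reaches 5 years. Under uniform accrual this is about 0.5 to 1.0 year later.
- State in Table 2 that the 5-year EPIC-26 is the score nearest each man's own 5-year date within a set window, and fix that window before the data are drawn.
- State that 5-year disease control will be reported by an estimate that allows for censoring.

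The cost is one extra registry extract, a few lines of wording and a somewhat later final secondary report. No participant procedure changes.

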**Fig. 3 Fig3:**
[figure not shown]
**a and b.** ArteraAI Prostate Test report examples. Green box highlighting the prognostic model score and Blue box highlighting the predictive model result for ADT benefit

**Table 2 Tab2:** Schedule of assessments (according to SPIRIT-AI extension)

	Enrolment / Pre-test^1^	Post-test^2^	5-year follow-up
1. Demographics	X		
2. Prostate cancer history	X		
3. Shared ADT decision recommendation as determined by primary clinician and participant	X	X	
4. EPIC-26 Quality of Life questionnaire	X^*3*^		X^*3*^
5. Disease Control			X^*3*^

^*1*^
*Enrolment / pre-test can happen over a period of 14 days*

^*2*^
*Post-test data collection may occur at initial consult if ArteraAI Prostate Test results are available*

^*3*^
*Data linkage through Prostate Cancer Outcomes Registry at median 5-year follow-up.*

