The ArteraAI Prostate Test is a unique clinicopathological biomarker test which utilises the MMAI architecture described to run two models: a prognostic model and a predictive model. Firstly, the prognostic model provides estimates of distant metastasis (DM) and prostate cancer-specific mortality (PCSM) risk. The prognostic deep learning model was trained and validated on 5 phase III randomised control trials (NRG/RTOG 9202, 9408, 9413, 9910, and 0126), with a total of 5,654 patients and a dataset of 16,204 histopathology slides. This model was shown to significantly outperform the NCCN classification with a 5-year distant metastasis AUC of 0.83 compared to 0.72 for NCCN, *p* < 0.001 [14]. The predictive model assesses the benefit of short-term, 4–6 months of ADT (ST-ADT) in intermediate-risk (IR) prostate cancer patients and has recently been validated. In the predictive model positive patients, ST-ADT significantly reduced the risk of distant metastasis compared to radiotherapy alone (sHR = 0.34, 95% CI 0.19–0.63, *p* < 0.001). There were no significant differences with the addition of ADT in the predictive model negative subgroup (sHR = 0.92, 95% CI 0.59–1.43, *p* = 0.71) [15].

The test can inform the shared ST-ADT discussion between clinicians and patients on the benefit ADT may have in men being managed with definitive RT for IR prostate cancer. The real-world data on the impact of this test in clinical practice is currently lacking, which is the main question we are exploring via ASTuTE.

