**PCS III** [28]	400 IR men	76 Gy / 38 fractions ± 6 months of LHRH agonist with bicalutamide	10 years PCSM 6.5% woST-ADT 1.5% wST-ADT DM 10% woST-ADT 3.5%% wST-ADT	-78% UIR -contained another randomisation arm of 70 Gy / 35 fractions wST-ADT, 200 IR men.

*Abbreviations*: IR - intermediate risk, LHRH - Luteinizing hormone–releasing hormone, bcF - biochemical failure, woST - ADT–without short–term androgen deprivation therapy, wST - ADT–with short–term androgen deprivation therapy, DSM - disease specific mortality, PCSM - prostate cancer specific mortality, FIR - favourable intermediate risk, UIR - unfavourable intermediate risk, DM - distant metastasis, OS - overall survival

Around 70% of men recover their testosterone from 6 months of ADT at 1.5 years from initial injection [29]. This is a lengthy time for reduced QoL and toxicity effects with some patients taking longer, or never recovering [30–33]. D’Amico et al. helped highlight the potential deleterious effects of ST-ADT in patients with moderate or severe comorbidity [11]. Although some of the effects on bone health and lean muscle mass can be proactively managed through serial DEXA imaging and exercise medicine, ideally only men most likely to derive meaningful benefit from ST-ADT would be exposed to these toxicities in the first place.

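### The only scheduled post-treatment EPIC-26 score, at 5 years, falls well after the period in which the article itself places the quality-of-life loss from short-term ADT

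*Protocol article*

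**What the plan says.** The Endpoints section names the instrument: "The secondary endpoint of quality of life will be assessed using the Expanded Prostate Cancer Index Composite questionnaire (EPIC-26"). It gives no time point for quality of life, although it fixes efficacy at 5 years. The secondary hypothesis in the same section expects "improved quality of life for those spared ADT".

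Table 2 supplies the times. Its row "4. EPIC-26 Quality of Life questionnaire" has a mark under enrolment/pre-test and a mark under 5-year follow-up. The post-test cell is empty, and the table has no column between post-test and 5 years. Both marks carry footnote 3: "Data linkage through Prostate Cancer Outcomes Registry at median 5-year follow-up". The Methods section agrees: "At a median follow-up of 5 years for the cohort, a data linkage with PCOR will be established".

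On the course of the ADT effect, the Background gives the treatment length: "The predictive model assesses the benefit of short-term, 4–6 months of ADT (ST-ADT"). The Discussion then states: "Around 70% of men recover their testosterone from 6 months of ADT at 1.5 years from initial injection". It continues: "This is a lengthy time for reduced QoL and toxicity effects", and adds that recovery is slower in some men and never comes in others.

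**The concern.** The article says when quality of life suffers under short-term ADT, and then schedules its only post-treatment measurement long after that period has ended for most men. The hypothesis is about men spared ADT in general and is not limited to lasting harm.

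At stake is what the secondary result can mean. If the harm is largely transient, two groups that differed clearly in the first year or so could look alike at 5 years. A null finding would then be uninformative about the benefit the trial hopes to show, which is less overtreatment with better quality of life, yet it could easily be read as evidence against that benefit.

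**Working it through.** The plan states no effect size, standard deviation, power or sample size for EPIC-26, so there is no figure of its own to reproduce. The check compares dates and then illustrates dilution.

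**Timeline, from the document**
- Length of ADT: 4–6 months (Background); the recovery figure refers to 6 months (Discussion).
- About 70% recovered at 1.5 years from the first injection, so 1 − 0.70 = 0.30 not recovered.
- With 6 months of ADT, that point is 1.5 − 0.5 = 1.0 year after ADT ends.
- Only post-treatment EPIC-26 mark: 5 years. Gap after the 70% point: 5 − 1.5 = 3.5 years, taking the first injection as close to enrolment.
- Five years is a cohort median. With accrual from December 2023 to an expected end in 2025, individual follow-up at that time spreads by about a year either side. Even at 4 years the gap is 4 − 1.5 = 2.5 years.

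The ordering is therefore clear from the article alone: the score is taken well after most men have recovered.

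**Dilution, illustrative only**

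Let f be the fraction of the on-treatment mean difference that remains at 5 years. For fixed power the required sample scales as 1/f². The document does not give f. Possible values:

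| f | Assumption | Sample multiplier 1/f² |
|---|---|---|
| 0.50 | some loss outlasts testosterone recovery | 4.0 |
| 0.30 | all-or-none loss, carried only by the 30% unrecovered at 1.5 years | 11.1 |
| 0.15 | as above, with half of those recovering later | 44.4 |

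The next table assumes a standardised on-treatment difference d, two-sided alpha 0.05 and 80% power, with n per group = 2(1.960 + 0.842)² / (f·d)². Power is also shown for an assumed 200 v 200 men.

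| d (assumed) | n per group, f = 1 | n per group, f = 0.30 | n per group, f = 0.15 | Power 200 v 200, f = 1 | Power, f = 0.30 | Power, f = 0.15 |
|---|---|---|---|---|---|---|
| 0.3 | 175 | 1938 | 7752 | 85% | 15% | 7% |
| 0.5 | 63 | 698 | 2791 | >99% | 32% | 11% |
| 0.8 | 25 | 273 | 1091 | >99% | 67% | 22% |

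With 400 v 400, which would use all 800 planned men in equal groups, power at f = 0.30 is 25%, 56% and 92% for d = 0.3, 0.5 and 0.8. A large initial effect could thus still be visible at 5 years; a small or moderate one probably would not.

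**The case against.** The strongest reply is that footnote 3 and the Methods section date the linkage, not the questionnaires. The enrolment score carries the same footnote, so the linkage must retrieve scores recorded years before. One extract at year 5 could equally return scores from the first year or two, if the registry holds them. This stands: the document does not show that such scores are absent, and it is why the first remedy is an extraction. It does not remove the mismatch, because Table 2 is an explicit schedule and names only two times.

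Second, the Discussion part of the Abstract places quality of life in the medium term, so a 5-year measure may be intended. That is fair as a statement of scope. The hypothesis in Endpoints carries no such limit, however, and if only lasting differences are meant it should say so.

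Third, the study is described as hypothesis-generating and has no power target for quality of life, so a sample multiplier has nothing to be compared with. This too stands: the multiplier shows how sensitive the comparison is and does not measure a shortfall. A descriptive summary taken outside the effect period can still mislead.

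A reader might go further and infer that 0.3 is a ceiling on the remaining effect. The document does not support that. It reports testosterone recovery and no EPIC-26 time course, and it mentions bone and muscle effects as well as men who never recover. Loss that outlasts hormonal recovery would leave more than 0.3.

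A reader might also infer from footnote 3 that the baseline score is lost. Nothing in the article suggests this; the registry may well have recorded it at the time. It only needs confirming.

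**Conclusion.** The point holds as a mismatch between a stated hypothesis and a fixed schedule. Followed as written, the plan measures quality of life after treatment once, about 3.5 years after the time by which about 70% of men have recovered testosterone. That score is likely to miss much of the ADT-related difference and can mainly show persistent effects. A null at 5 years would not show that sparing ADT brings no quality-of-life gain.

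This rests on the article's own link between the recovery period and reduced quality of life. The amount lost cannot be derived from the document. The figures of 0.3 of the effect and 11 times the sample apply only if the loss is all-or-none and tracks testosterone non-recovery. It would be too strong to say that the trial cannot address quality of life at all: lasting differences remain measurable, and earlier registry scores may exist. The primary endpoint is not affected.

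**What to change.** 1. At the linkage already planned, also extract any EPIC-26 score recorded within about the first 1.5 years. Pre-specify the time window now, make that score the main quality-of-life comparison, and keep 5 years as the long-term measure. Amend Table 2 to name the registry time points.
2. If the registry holds no such score, choose between adding one short questionnaire for men still inside the window and restating the hypothesis as a persistent quality-of-life difference at 5 years.
3. Confirm that the registry's baseline EPIC-26 is recorded before treatment starts.

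Cost: items 1 and 3 need a slightly larger extract, a query to the registry and a short amendment. A new questionnaire costs more, since Table 2 shows no study contact between post-test and linkage. It would also reach only part of the cohort: if ADT starts near enrolment, a man enrolled in December 2023 leaves the 1.5-year window around mid-2025, and one enrolled at the end of 2025 around mid-2027. Restating the hypothesis costs nothing but narrows what the trial can claim.
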